### Statistical analysis

The co-primary outcomes – whether the antibiotic was filled and taken and whether the parent was ‘very’ or ‘extremely satisfied’ with their child’s care – will be analyzed with a logistic mixed effects regression model. This model accounts for the hierarchical structure of the data with patients nested within clinics. The primary analysis will include covariates for the intervention group, the random effect for clinic, and pre-specified confounding factors including age, race, gender, ethnicity, language preference, and insurance type. Any variables that appear unbalanced between the study arms at *p* < 0.2 will also be included as predictors. Since it is possible that clinicians (within clinics) are another source of variation, an additional random effect for clinician within practices will be included if there is evidence of sufficient variability at this level. Multiple comparisons in testing the co-primary outcomes will be accounted for with an alpha = 0.025 to assess statistical significance. All other hypothesis tests will be two-sided with a significance level of 0.05.

Secondary outcomes (Table 1) will be analyzed using linear or logistic mixed effects regression, as appropriate. Similar random effects will be included accounting for the nested structure of the data. Secondary analysis results will be expressed as mean differences and regression coefficients or differences in proportion and odds ratios, as appropriate, with 95% confidence intervals (CIs).

Exploratory analyses will be conducted to test for potential effect modification by select patient characteristics. The effects of the health systems-level and hybrid interventions on antibiotic prescribing and parent satisfaction may differ based on race, ethnicity, insurance type, and clinical setting. Logistic mixed effects regression will be used including a main effect for the moderator and an interaction between the moderator and intervention variable. Due to the exploratory nature of these analyses, p-values will not be adjusted for multiple comparisons, however all subgroup analyses will be reported.

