## Methods

### Overview of study design

 This will be a pragmatic, cluster-randomized controlled trial that will use a hybrid implementation-effectiveness design [31]. The effectiveness and implementation outcomes of a “gold standard” [32] health systems-level intervention and a hybrid health systems-level plus shared decision-making intervention will be compared using the Practical Robust Implementation and Sustainability Model (PRISM) [33] and Reach Effectiveness Adoption Implementation Maintenance (RE-AIM) frameworks [34]. Participating clinics will be randomly assigned to one of the two interventions (Fig. 1) using covariate-constrained randomization. The primary outcomes of the study are 1) parent satisfaction with their child’s treatment for AOM, and 2) antibiotic courses *taken* by children with AOM by parent report. Secondary outcomes include 1) shared decision-making process and effectiveness [35, 36], 2) pediatric quality of life [14], 3) symptom severity and duration [22, 37, 38], 4) missed work, school, and daycare, 5) adverse drug events [14], 6) treatment failure [25, 39], 7) management strategy used (immediate antibiotic versus watchful waiting), and 8) whether or not an antibiotic prescription was filled at a pharmacy (Table 1).

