Implementation and sustainability infrastructure	• Current resources and resource utilization for AOM management (e.g., EHR-tools, education materials) and stewardship • Baseline workflow for AOM • Perceived facilitators/barriers to sustainability	• Key informant interviews (clinicians and administrators) • Process mapping interviews (clinicians and administrators)	• Adapt sustainability plan and EHR workflow • Develop workflow for SDM (Hybrid only)
Organizational characteristics	• Existing collaborations and information flow between clinics • Administrative support • Shared goals	• Key informant interviews (clinicians and administrators)	• Modify communication plan and add administrative support if needed
Patient characteristics	• Demographics • Urban, suburban, rural designation	• EHR data collection • Clinic zip codes	• Use data for covariate-constrained cluster randomization

^a^
*HEDIS* Healthcare effectiveness data and information set

Contextual factors will be assessed at the child/parent, clinician, clinic, and health systems-levels using key informant semi-structured interviews and focus groups, process mapping, and electronic health record (EHR) data. Semi-structured key informant interviews will be conducted with a convenience sample of clinic administrators and clinicians across participating clinics to understand 1) typical workflow of visits for children with AOM, 2) contextual factors that may facilitate or impede use of watchful waiting, 3) contextual factors that may facilitate or impede implementation of intervention components, and 4) organization culture. To understand parent perspectives of factors that may facilitate or impede the acceptance of watchful waiting, focus groups of a convenience sample of parents from each site will be conducted.

Finally, to better understand variability in care, assist with setting targets for improvement, and inform the randomization of clinics, baseline EHR data will be abstracted to evaluate pre-intervention antibiotic prescribing patterns and patient-level characteristics from potential participating clinics. Substantial efforts will be made to minimize missing data on predictors by abstracting data from multiple EHR locations. For missingness of key predictors, sensitivity analyses will be carried out using multiple imputation approaches [41].

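### The primary model names no clinic-level variable used in the constrained randomisation, and its p<0.2 rule tends to keep such variables out; this can cost power

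*Protocol article*

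**What the plan says.** **Allocation.** Overview of study design: "Participating clinics will be randomly assigned to one of the two interventions (Fig. 1) using covariate-constrained randomization".

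**Inputs to the allocation.** Under Formative evaluation of context with PRISM, the patient-characteristics row of Table 3 lists demographics and "Urban, suburban, rural designation". It gives their purpose as "Use data for covariate-constrained cluster randomization". The text below the table adds a further aim, to "inform the randomization of clinics, baseline EHR data will be abstracted to evaluate pre-intervention antibiotic prescribing patterns and patient-level characteristics". The article does not print a final list of constraint variables. Health system is not described anywhere as a constraint or stratification factor.

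**Primary model.** Statistical analysis specifies a logistic mixed model with intervention group, a random effect for clinic, and "pre-specified confounding factors including age, race, gender, ethnicity, language preference, and insurance type". Variables that look unbalanced between arms at p<0.2 "will also be included as predictors". A random effect for clinician may be added. No clinic-level covariate is named.

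**The concern.** Constrained randomisation removes from the arm contrast the part of between-clinic variation that the chosen variables explain. A model that omits those variables still counts that variation in its standard error. If the variables are prognostic, the standard error is then larger than the true sampling variability under the design. The test rejects less often than its nominal level, and the precision bought by the constraint is not used.

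The p<0.2 rule works against the design. It admits a variable when the arms differ on it, and the constraint exists to make them alike. Setting, which Table 3 ties to the constraint, is therefore among the variables least likely to enter. The same holds for baseline prescribing if it is constrained.

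With 33 clinics, between-clinic variance is a large part of the total, so the choice could matter for both co-primary outcomes, each tested at 0.025.

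**Working it through.** **Inputs from the article.** 33 clinics (10, 9 and 14 by health system); 1,566 children; ICC 0.02 to 0.05; two-sided alpha 0.025; 12% antibiotic taken and 76% satisfied in the health systems-level arm; detectable differences of 8 and 11 points (antibiotic) and 9 and 12 points (satisfaction).

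**1. Reproduce the plan's power.** m = 1,566/33 = 47.45 and DE = 1 + (m − 1) × ICC.
- ICC 0.02: DE = 1.929, effective n per arm = 783/1.929 = 405.9.
- ICC 0.05: DE = 3.323, effective n per arm = 783/3.323 = 235.6.

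Power = Φ[(Δ − 2.241 × SE0)/SE1], with SE0 pooled and SE1 unpooled. For 12% vs 20% at ICC 0.02:
- SE0 = √(2 × 0.16 × 0.84/405.9) = 0.02573
- SE1 = √((0.12 × 0.88 + 0.20 × 0.80)/405.9) = 0.02558
- power = Φ(0.873) = 0.809

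For 12% vs 23% at ICC 0.05, power is 0.819. For satisfaction, 76% vs 85% gives 0.842 and 76% vs 88% gives 0.878. The stated 80% is reproduced (for the antibiotic outcome, as an increase from 12%). The calculation uses no covariates, so it does not depend on the variables at issue.

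**2. How much variance could be recovered.** The between-clinic share of the variance of a clinic mean is ICC/[ICC + (1 − ICC)/m].
- ICC 0.02: 0.02/(0.02 + 0.98/47.45) = 0.49
- ICC 0.05: 0.05/(0.05 + 0.95/47.45) = 0.71

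Variables explaining a share R² of between-clinic variance remove at most R² times these figures. At R² = 0.3 that is about 15% and 21%.

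**3. Simulation.** Clinic means, 16 vs 17 clinics. The allocation is drawn from the best 10% of 300 candidates. Between-clinic variance is ICC × p̄(1 − p̄). Its explained part R² is split equally between one clinic covariate and health system. The unadjusted model has arm only; the adjusted model adds the covariate and two system indicators. Tests use a t reference at 0.025. R² is assumed, because the documents give no value. There are 4,000 replicates for type I error and 2,000 for power.

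Antibiotic outcome, covariate and system both constrained:

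| ICC | R² | Type I, unadjusted | Type I, adjusted | Power, unadjusted | Power, adjusted |
|---|---|---|---|---|---|
| 0.02 | 0 | 0.025 | 0.026 | 0.784 | 0.774 |
| 0.02 | 0.3 | 0.016 | 0.026 | 0.783 | 0.822 |
| 0.02 | 0.6 | 0.011 | 0.026 | 0.791 | 0.888 |
| 0.05 | 0 | 0.029 | 0.029 | 0.774 | 0.769 |
| 0.05 | 0.3 | 0.011 | 0.021 | 0.800 | 0.870 |
| 0.05 | 0.6 | 0.004 | 0.026 | 0.844 | 0.962 |

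At R² = 0.3 the gain is 3.9 points (ICC 0.02) and 7.0 points (ICC 0.05). Satisfaction behaves alike: at R² = 0.3, type I error is 0.018 and 0.014 unadjusted, and power rises from 0.820 to 0.862 and from 0.861 to 0.907.

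**4. System not constrained.** This is closer to what the article documents (5,000 replicates for type I error, 2,500 for power; results in the order ICC 0.02, ICC 0.05).
- R² = 0.3: type I error unadjusted is 0.017 and 0.019; power goes from 0.773 to 0.799 and from 0.774 to 0.848.
- R² = 0.1: type I error unadjusted is 0.022 and 0.023; power goes from 0.767 to 0.752 and from 0.775 to 0.762, a loss of 1.5 and 1.3 points.
- R² = 0: power goes from 0.756 to 0.719 and from 0.783 to 0.742, a loss of 3.7 and 4.1 points. With system balanced, the loss at R² = 0 was only 1.0 and 0.5 points, so most of this cost comes from carrying unbalanced system indicators that explain nothing.

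**5. Reference distribution.** In the setting of step 4 at R² = 0.3, a normal (Wald z) reference gives unadjusted type I error of 0.024 and 0.027, and adjusted 0.031 and 0.038. The conservatism in step 3 is therefore specific to a t reference.

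**The case against.** **The planned model is not the unadjusted one simulated.** It carries age, race, gender, ethnicity, language and insurance, and demographics are one of the two items in the constraint row of Table 3. Part of the constraint is thus already adjusted for at child level. This stands: what matters is the variance that clinic-level variables explain beyond those covariates, so the simulated effects are likely to be upper figures for a given R².

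**The list may be open.** It is introduced by the word including, and the full covariate and constraint lists may sit in an analysis plan that is not shown. This stands in part. But every example given is child-level, and the p<0.2 rule is a stated choice that pushes the wrong way.

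**Baseline prescribing may be a weak predictor.** The Background puts antibiotic prescribing at about 95% when the condition is diagnosed, so clinics may differ little. The outcome is antibiotic taken, after both arms have received a prescribing intervention. The article also says only that these data inform the randomisation. This stands, so that variable belongs in the model only if it is actually constrained.

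**Stronger readings.** A reader might infer that the trial is underpowered, or that its test is certainly conservative. The documents support neither: the 80% assumed no covariates, and conservatism depends on an unknown R² and on the reference distribution. A reader might also point to health system, where public insurance is 74.5%, 88.1% and 18.8%. But insurance type is already in the model and system is not documented as constrained, so for system the argument is one of precision only.

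**Conclusion.** The mismatch between design and analysis is real and documented. At least one clinic-level constraint variable, setting, is absent from the named model terms, and the stated rule for adding terms tends to leave it out. The consequence is conditional. With an assumed 30% of between-clinic variance explained, type I error for the antibiotic outcome falls to about 1.1 to 1.6% and adjustment adds about 4 to 7 points of power. At 10% there is little or no gain, or a loss of up to about 2 points. At zero the loss can reach about 4 points if unbalanced system indicators are added as well.

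These figures rest on a linear clinic-level approximation with a t reference, no child covariates, and (for the 1.1 to 1.6%) system treated as balanced along with the covariate. With system unconstrained, the corresponding type I error is 1.7 to 1.9%. This is an efficiency point. Neither the validity of the trial nor its stated power is in question.

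**What to change.** In the Statistical analysis section:
- Pre-specify as fixed effects in the primary model every clinic-level variable actually used in the constraint: at least urban/suburban/rural setting, and the clinic's baseline immediate-antibiotic rate if it is used.
- Remove the p<0.2 balance-test rule, so that the adjustment set is fixed before outcome data are seen.
- Treat health system as optional, for precision only. It overlaps with setting (all nine Denver clinics are urban), and its indicators cost power if they explain little.
- Pair the adjusted model with a reference distribution suited to 33 clinics. In the simulation, adjustment with a normal reference raised type I error to 3.1 to 3.8%. The analysis plan is the natural place for this detail.

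The cost is a change of wording and a few cluster-level degrees of freedom. Setting and baseline prescribing are already to be collected before randomisation, and the article states that recruitment has not begun.

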### Study setting and population

A total of 33 clinics from three geographically disparate health systems – AllianceChicago (AC) (a network of community health centers in Chicago, IL, USA), Denver Health and Hospital Authority (DHHA) (Denver, CO, USA), and Intermountain Health (IH) (Salt Lake City, UT, USA) – will be randomized. The participating clinics include over 200 pediatric, family medicine, and urgent care clinicians who serve more than 6,000 children with AOM annually (Table 2). The participating sites were selected to represent a diverse population that includes children of different races, ethnicities, language preferences, and socioeconomic statuses. Because most antibiotics for children in the United States are prescribed in non-academic settings, all participating clinics are community-based to increase the generalizability of study findings [21, 40].

**Table 2 Tab2:** Aggregate data of clinic and patient characteristics for each participating site

**Clinic Characteristics**	**Alliance Chicago N (%)**	**Denver Health and Hospital Authority N (%)**	**Intermountain Healthcare N (%)**
Clinics to be randomized	10	9	14
Total eligible clinics	45	33	31
Family Medicine	0	7	0
Pediatric	0	23	0
Urgent Care	0	3	31
Hybrid (multi-specialty)	45	0	0
Clinical setting (participating)			
Urban	TBD	9 (100)	3 (10)
Suburban	TBD	0 (0)	24 (77)
Rural	TBD	0 (0)	4 (13)
Clinicians per clinic (mean eligible clinicians, range)	20.3 (3–51)	22.1(10–38)	29.3 (2–60)
Clinician Type			
Physician	TBD	123 (61.8)	205 (71.9)
Advanced Practice Provider	TBD	43(21.6)	80 (28.1)
Annual acute otitis media encounters per clinic (mean, range)	382 (121–1172)	228 (40–468)	346 (2–944)
**Patient Demographics**^a^	**N (%)** ***N***** = 12,449**	**N (%)** ***N***** = 7,524**	**N (%)** ***N***** = 12,818**
Age (mean ± standard deviation, years)	4.3 (± 3.9)	3.4 (± 3.1)	5.2 (± 4.5)
Race			
American Indian/Alaskan Native	50 (0.4)	60 (0.8%)	91 (0.7%)
Asian	336 (2.7)	278 (3.7%)	152 (1.2%)
Black/African American	2042 (16.4)	1091 (14.5%)	163 (1.3%)
Native Hawaiian/Pacific Islander	212 (1.7)	45 (0.6%)	266 (2.1%)
White	7718 (62.0)	5477 (72.8%)	11,695 (91.2%)
Other/Unknown	2104 (16.9)	579 (7.7%)	451 (3.5%)
Ethnicity			
Hispanic/Latinx	7656 (61.5)	5116 (68.0%)	1,939 (15.1%)
Non-Hispanic/Latinx	4431 (35.6)	2408 (32.0%)	10,644 (83.1%)
Declined/Unknown			234 (1.8%)
Language Preference			
English	7108 (57.1)	4703 (62.5%)	12,556 (98.0%)
Spanish	5041 (40.5)	2332 (31.0%)	225 (1.8%)

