### Patient eligibility, enrollment, and data collection

Children aged 6 months-17 years old treated for uncomplicated AOM at a participating clinic during the study period will be prospectively identified. Trained research staff will contact the parents of potentially eligible children via telephone, electronic mail, or the EHR and screen for eligibility. Children who received any antibiotic within 30 days prior to the visit, have a history of tympanostomy tubes, have current tympanic membrane perforation, or have a concomitant diagnosis that may warrant an antibiotic (e.g., Group A streptococcal pharyngitis, pneumonia) will be excluded. For children meeting all eligibility criteria, informed consent will be obtained from the parents (with assent from the child when appropriate) by trained research personnel. An example of the informed consent form can be found in the Supplement. Upon enrollment, the parents will complete a survey where the following data will be collected: demographic characteristics of the child (age, sex, race, ethnicity, language preference, insurance type), vaccination status, and treatment strategy used at the visit (observation, delayed antibiotic prescription, or immediate prescription). Ten days after enrollment, the parents will complete a second survey assessing whether any antibiotics that were prescribed were ultimately filled and taken, clinical encounters occurring after the index visit, new antibiotics prescribed within 30 days after the index visit, and their satisfaction with their child’s care.

To prevent potential imbalances in the number of children enrolled from a given clinic, there will be maximum number of children that can be enrolled from each clinic each month. Furthermore, there will be enrollment targets for race/ethnicity, preferred language, and insurance status. Participant recruitment has not yet begun (Table 5).

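### The primary model takes in any variable that differs between arms at p < 0.2, so its covariates are chosen by significance test and variables the intervention is meant to change are not excluded

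*Protocol article*

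**What the plan says.** In the protocol article, Statistical analysis, the co-primary outcomes are analysed with a logistic mixed model containing intervention group, a random clinic effect and "pre-specified confounding factors including age, race, gender, ethnicity, language preference, and insurance type". The next sentence extends the model: "Any variables that appear unbalanced between the study arms at" p < "0.2 will also be included as predictors". It does not name candidates, does not restrict them to baseline, and does not say whether the balance test allows for clustering.

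Four other places bear on this rule:

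- Overview of study design: "Participating clinics will be randomly assigned to one of the two interventions", "using covariate-constrained randomization". Table 3 adds that patient demographics and urban, suburban or rural designation feed that randomisation.
- Patient eligibility, enrollment, and data collection: children are identified after being treated at a participating clinic. The enrolment survey records demographics, vaccination status and, beside them, "treatment strategy used at the visit (observation, delayed antibiotic prescription, or immediate prescription".
- Overview of study design: the secondary outcomes include "management strategy used (immediate antibiotic versus watchful waiting". Table 1 marks it as a process measure at day 0.
- Table 1 also lists a shared decision-making score at day 0 as a process measure.

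**The concern.** There are two separate weaknesses.

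**Selection by p-value.** A covariate deserves a place in the model because it predicts the outcome. A between-arm p-value says nothing about that; it reacts to chance differences and to sample size. The rule is stated in advance, but the model it produces is not known until data have been compared by arm.

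**No bar on post-randomisation variables.** Clinics are randomised first and children enrol later, so every child-level variable is recorded after randomisation. Most, such as age or language, cannot be changed by the intervention. Treatment strategy and the shared decision-making score can be, and both interventions exist to change how the visit is handled. Strategy lies on the path from intervention to antibiotic taken, and it tends to differ between arms when one intervention changes prescribing more than the other. A model that adjusts for it no longer estimates the whole effect of the intervention on that co-primary outcome.

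**Working it through.** **Inputs from the protocol article.** 33 clinics; total N 1,566; outcome ICC 0.02 to 0.05; two-sided alpha 0.025; 12% taking an antibiotic in the health systems-level arm. Mean cluster size m = 1,566 / 33 = 47.45. Design effect = 1 + (m − 1) × ICC = 1.929 at ICC 0.02 and 3.323 at ICC 0.05.

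**The plan's own figure.** With these inputs and a two-proportion test, 12% against 20% at ICC 0.02 needs N = 1,536 (power 80.9% at 1,566), and 12% against 23% at ICC 0.05 needs N = 1,502 (power 81.9%). The stated 1,566 is reproduced closely. The covariate rule does not affect it.

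**1. How often does the rule fire by chance?** With a correctly sized test, each balanced candidate is flagged 20% of the time. For k independent candidates, P(at least one) = 1 − 0.8^k: 49% for k = 3, 67% for k = 5, 89% for k = 10.

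If the test ignores clustering, P(flag) = 2 × [1 − Φ(1.2816 / √(1 + 46.45 × ICC of the covariate))]:

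| Assumed covariate ICC | P(flag) |
|---|---|
| 0.05 | 48% |
| 0.10 | 59% |
| 0.20 | 69% |
| 0.30 | 74% |

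These covariate ICCs are assumptions, and the formula takes unconstrained allocation.

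**2. Would strategy be flagged?** At outcome ICC 0.02 the effective size per arm is 783 / 1.929 = 405.9. For an assumed 30% against 20% immediate prescribing, SE = √((0.21 + 0.16) / 405.9) = 0.0302, z = 3.31, and P(flag) = Φ(3.31 − 1.28) = 98%. For 50% against 40% the same steps give about 94%.

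**3. What would adjusting for strategy do to antibiotic taken?** On the risk-difference scale, the part that runs through strategy is (difference in proportion given an immediate prescription) × (P(taken | immediate) − P(taken | watchful waiting)). Adjustment removes this part and keeps any difference between arms within a strategy. Assume full mediation, with antibiotic taken in 90% after an immediate prescription and 3% after watchful waiting:

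- Immediate prescription 10% against 1.5%: antibiotic taken is 0.10 × 0.90 + 0.90 × 0.03 = 11.7% against 0.015 × 0.90 + 0.985 × 0.03 = 4.3%. The difference, −7.4 points, equals −0.085 × 0.87, so all of it is removed.
- Immediate prescription 20% against 10.5%: 20.4% against 12.1%. The difference, −8.3 points, equals −0.095 × 0.87, and again all of it is removed.

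A simulation used 1,000 trials per scenario, 33 clinics of 47 children, ICC 0.02, and logistic regression with cluster-robust errors standing in for the mixed model:

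| Scenario | Flagged at p < 0.2 | OR without strategy | Rejection without strategy | OR under the rule | Rejection under the rule |
|---|---|---|---|---|---|
| about 12% vs 4% | 100% | 0.33 | 100% | 1.01 | 2.8% |
| about 21% vs 12% | 99.9% | 0.54 | 96% | 0.99 | 2.9% |

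Partial mediation gives partial attenuation.

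**4. Type I error when the covariate cannot be affected by the intervention.** A simulation used 33 clinics of 47, outcome ICC 0.02, a continuous outcome, a balance test ignoring clustering, 8,000 trials per setting and nominal 2.5%. The rule rejected in 2.3% and 2.0% (covariate ICC 0.05; slopes 0.2 and 0.5) and in 2.0% and 1.5% (covariate ICC 0.20; same slopes). Monte Carlo error is about √(0.025 × 0.975 / 8,000) = 0.17 points. A separate simulation gave about 1.5% to 2.2%. A check with a REML mixed model showed the same pattern: near nominal with the weaker slope, below it with the stronger, no material inflation.

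**The case against.** The rule directly follows a list of confounders and says that further variables will also be included, so the natural reading is more baseline characteristics. Management strategy is classed as a secondary outcome and has its own analysis. Taken wholly literally, the sentence would admit day-10 outcomes as predictors, which nobody intends. A candidate list and the form of the balance test may be in a statistical analysis plan that is not shown. Children are also enrolled after clinics are randomised, so differential recruitment can create real imbalance, and adjusting for it is reasonable.

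Much of this stands. It rules out several stronger conclusions a reader might infer:

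- *That the co-primary effect will be driven to zero.* This needs the literal reading and full mediation. Shared decision-making could also change whether parents give a delayed antibiotic, and adjustment for strategy would not remove that part. The argument covers antibiotic taken only; the documents show no mediation of satisfaction by strategy.
- *That the error rate is inflated.* The simulations point the other way.
- *That chance flagging far exceeds 20%.* This holds only if the test ignores clustering, which the article does not say. Constrained randomisation lowers it for the variables it balances, and race, ethnicity, language and insurance are in the model regardless.
- *That day-0 symptom severity is an equally clear case.* It appears in Table 1 but not in the description of the enrolment survey, and nothing shows that the intervention changes it.

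The objection does not remove the selection rule itself, which the article states. Nor does it supply the missing limit: the survey that provides the baseline covariates also holds treatment strategy.

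**Conclusion.** The point holds in a limited form and should be fixed before outcome data are compared by arm. The primary covariate set is chosen by between-arm significance and known only after data by arm are seen. As worded, it does not exclude treatment strategy or the day-0 shared decision-making score.

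How much this matters depends on the reading. On the probable one (baseline variables only), the cost is a model not fixed in advance and, if the balance test ignores clustering, a mildly conservative test: about 1.5% to 2.3% against 2.5%, under assumed covariate ICCs and slopes. On the literal reading, the effect on antibiotic taken is attenuated in proportion to its mediation by strategy, and is lost entirely only if mediation is complete. The mediation scenarios use assumed prescribing and antibiotic-taking rates; the first is set to match the planned 12%. The sample size stands.

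**What to change.** Remove the p < 0.2 rule from the primary model and replace it with a fixed statement:

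- The covariates are the six already listed, the variables used in the constrained randomisation, and any other baseline prognostic variable already collected, such as vaccination status.
- No variable measured after clinic randomisation that the intervention can change enters the primary model. Name management strategy and the shared decision-making score as examples.
- Imbalance between arms is shown descriptively.
- Any imbalance-driven adjustment is a sensitivity analysis, restricted to named baseline variables. This still addresses recruitment imbalance after clinic randomisation.

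The cost is a few sentences in the protocol and analysis plan, with no new data and no change in sample size. The downside is slightly less freedom to react to chance or recruitment imbalance in the primary model. The article states that recruitment had not begun, so the change could be made before any outcome data existed.

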### Sample size and power

In the health systems-level intervention group, it is estimated the baseline proportion of cases where an antibiotic is taken will be 12% [19, 23, 24, 30] and 76% of parents will report being very or extremely satisfied [29]. Given the cluster design and co-primary outcomes, the sample size calculation used an intraclass correlation coefficient (ICC) of 0.02 to 0.05 for within-clinic correlation and a two-sided test with alpha = 0.025 to account for multiple comparisons. A total sample size of 1,566 children will be required to provide 80% power to detect an absolute difference in antibiotic courses taken of between 8% (ICC = 0.02) and 11% (ICC = 0.05) and an absolute difference in the proportion of parents satisfied between 9% (ICC = 0.02) and 12% (ICC = 0.05) when comparing the two intervention groups. Based on preliminary data from the 33 participating clinics, it is estimated there will be 27,997 eligible children across the sites over 3 years. With a projected 16% enrollment rate and 7% attrition rate [46], up to 4,100 children could successfully complete the study, well-exceeding the enrollment target of 1,566 children.

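### Testing both primary outcomes at a fixed 0.025 is valid, but the Holm procedure is never less powerful at the same 5% family-wise error

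*Protocol article*

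**What the plan says.** The Statistical analysis section of the protocol article names two co-primary outcomes: "whether the antibiotic was filled and taken and whether the parent was ‘very’ or ‘extremely satisfied’ with their child’s care". It fixes the decision rule for them: "Multiple comparisons in testing the co-primary outcomes will be accounted for with an alpha = 0.025 to assess statistical significance".

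The Sample size and power section uses the same threshold, "a two-sided test with alpha = 0.025 to account for multiple comparisons", and concludes: "A total sample size of 1,566 children will be required to provide 80% power".

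No step-down, alpha-recycling or hierarchical rule appears. The article does not say whether the trial succeeds on either outcome or only on both. Splitting alpha implies that either suffices.

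**The concern.** Under the fixed rule each outcome is judged at 0.025 whatever the other shows. If antibiotic use differed clearly between the arms and satisfaction gave p = 0.04, satisfaction would have to be called non-significant. Holm would allow the claim at the same 5% family-wise level, with no extra children, no ordering of the outcomes and no assumption about how they are correlated.

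The Background and Discussion say that the interventions aim both to reduce antibiotic use and to raise satisfaction. A result on each is therefore of interest, and Holm's gain arises only when the other outcome succeeds. What is at stake is a few points of power for the second claim.

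**Working it through.** **1. Reproduce the plan's figure.** Inputs from Sample size and power: N = 1,566, two-sided alpha 0.025, reference rates 12% (antibiotic taken) and 76% (satisfied). The differences are 8 and 9 points at ICC 0.02, and 11 and 12 points at ICC 0.05. There are 33 clinics; equal arms and equal cluster sizes are assumed.

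- Mean cluster size: 1,566/33 = 47.45.
- Design effect 1 + (m − 1) × ICC: 1 + 46.45 × 0.02 = 1.93, and 1 + 46.45 × 0.05 = 3.32.
- Effective children per arm: 783/1.929 = 405.9, and 783/3.323 = 235.6.
- Power = Φ{[d√n − 2.2414 √(2p̄(1 − p̄))] / √(p₁(1 − p₁) + p₂(1 − p₂))}.
- Antibiotic, 12% to 20%, ICC 0.02: Φ[(1.612 − 1.162)/0.515] = Φ(0.87) = 80.9%. For 12% to 23%, ICC 0.05: 81.9%.
- Satisfaction, 76% to 85%, ICC 0.02: 84.2%. For 76% to 88%, ICC 0.05: 87.8%.

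The stated 80% is reproduced for the antibiotic outcome, and is somewhat conservative for satisfaction. With a t reference on 31 df at ICC 0.02 the powers are 77.6% and 81.1%. A common 80% is a fair starting point.

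**2. Error control.** Fixed split: 0.025 + 0.025 = 0.05. Holm with both nulls true: any rejection needs the smaller p-value at or below 0.025, which has probability at most 0.05. Holm with one null true: that null is rejected only if its own p-value is at or below 0.05. Neither step uses the dependence between the outcomes.

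**3. Gain when both effects are real.** With 80% power at 0.025 the expected test statistic is 2.2414 + 0.8416 = 3.083. Power at 0.05 is Φ(3.083 − 1.960) = 86.9%. If the tests are independent, Holm's power per outcome is 0.80 + (0.869 − 0.80) × 0.80 = 85.5%. Power for both is 0.64 + 2 × 0.80 × 0.0693 = 75.1%.

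For other correlations of the two test statistics, a bivariate-normal simulation gives the table below. It agrees with the closed form at correlation 0 to within 0.1 point.

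| Correlation (assumed) | Per outcome: fixed → Holm | Both: fixed → Holm | At least one: both rules |
|---|---|---|---|
| −0.5 | 80% → 86.5% | 60.9% → 73.9% | 99.2% |
| 0 | 80% → 85.6% | 64.1% → 75.1% | 96.0% |
| 0.5 | 80% → 84.6% | 68.8% → 77.9% | 91.3% |
| 0.8 | 80% → 83.8% | 73.0% → 80.4% | 87.1% |

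**4. The same at the plan's own inputs** (powers from step 1, correlation 0 to 0.5):

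- ICC 0.02: antibiotic 80.9% to 85.7–86.6%; satisfaction 84.2% to 87.9–88.9%; both 68.1–72.2% to 78.5–80.7%.
- ICC 0.05: antibiotic 81.9% to 86.9–87.6%; satisfaction 87.8% to 90.8–91.7%; both 71.9–75.4% to 81.5–83.3%.

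These rows take the antibiotic difference as an increase from 12%, the direction that reproduces 80%. For a decrease of the same size, which is what the interventions aim at, antibiotic power at 0.025 is already 97.6% (12% to 4%) or 99.6% (12% to 1%). Holm then mainly helps satisfaction: 84.2% to about 90%, or 87.8% to about 92.5%.

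**5. Only one real effect.** With independent tests, the real outcome gains 0.025 × 0.0693 = 0.0017, about 0.2 points. The null outcome's false-positive rate becomes 0.025 + 0.025 × 0.80 = 0.045, and reaches 0.050 if the other outcome is certain to be rejected. Under the fixed rule it is 0.025.

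**The case against.** The strongest reply is that nothing here is wrong. The split is valid and pre-specified, it is the one the trial was sized for, and the stated 80% power already pays for it. That stands: this is unused efficiency, and a sponsor could reasonably keep the present rule.

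Other parts of the reply also stand:

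- Independence is doubtful. Both outcomes come from the same parent on the same day-10 survey, so the gain has to be shown over a range.
- Holm gives up something. It keeps the family-wise error at 5%, but a lone null outcome is no longer held to 2.5%.
- The fixed split comes with simple 97.5% simultaneous intervals that always match the test. Under Holm, a second p-value between 0.025 and 0.05 is declared significant while its 97.5% interval includes no effect.
- If success required both outcomes, each could be tested at 0.05 and neither rule would be needed.

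A reader might infer that the trial forecasts a benefit of the hybrid arm on both outcomes. The documents do not say so. The Background and Discussion state aims shared by both interventions, and the sample-size section gives detectable differences, not expected effects. A reader might also infer that Holm justifies fewer children. It does not, because 80% power at 0.025 is what each outcome relies on when the other shows nothing.

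The reply does not remove the point. The article fixes the rule itself, and another rule with the same family-wise guarantee is never less powerful.

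**Conclusion.** An optional improvement, not an error. If both effects are real and each outcome has 80% power at 0.025, Holm adds about 4 to 6 points of power per outcome for correlations from 0.8 down to 0. It adds about 7 to 11 points for winning on both (11 at correlation 0, 9 at 0.5, 7 at 0.8). It adds nothing to the chance of winning on at least one, and about 0.2 points if only one effect is real.

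The sizes rest on an assumed correlation and a normal approximation. That Holm is never less powerful at the same 5% family-wise error rests on neither. A reader might take the fixed 0.025 as faulty error control or as inconsistent with the sample size. The documents do not support that: 0.025 + 0.025 = 0.05, and both sections use 0.025.

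**What to change.** Replace the multiplicity sentence in Statistical analysis, and its counterpart in any analysis plan, with:

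> The two primary outcomes will be tested with the Holm procedure at an overall two-sided 5% level (smaller p-value against 0.025; if significant, the other against 0.05); success on either outcome is claimed separately.

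Add that significance is judged by the Holm-adjusted p-values. State that 97.5% intervals are reported as conservative simultaneous intervals, which may include no effect when the second p-value lies between 0.025 and 0.05. Keep the sample size on 0.025.

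The cost is two or three sentences and no children. The downsides are the interval mismatch and the false-positive rate of up to 5%, not 2.5%, for a single null outcome when the other effect is real. The article says recruitment had not begun, so the change could be made before outcome data exist. Made after results are seen by arm, it would look data-driven.
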